**Discussion:**

This trial will assess the impact of a liberal versus conservative strategy of blood transfusion in a large cohort of critically ill patients with a primary acute brain injury. The results of this trial will help to improve blood product and transfusion use in this specific patient population and will provide additional data in some subgroups of patients at high risk of brain ischemia, such as those with intracranial hypertension or cerebral vasospasm.

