For patients with SAH, the following data are also collected: World Federation of Neurological Society (WFNS) score; Fisher CT-scan scale; ICP monitoring within the first 48 h; pupillary reactivity on arrival; hydrocephalus; diagnosis of vasospasm (either using trans-cranial Doppler [TCD], contrast CT scan, and/or angiography); development of delayed neurological ischemic deficit (DNID); therapies for DNID; and occurrence of DCI. TCD-vasospasm is defined as a mean flow velocity in any vessel > 200 cm/s or > 120 cm/s and a Lindegaard ratio > 3 [22]. Angiographic or contrast CT-scan vasospasm is defined by a neuroradiologist as moderate-to-severe arterial narrowing (> 50%) on specific imaging not attributable to atherosclerosis, catheter-induced spasm, or vessel hypoplasia. Definition of DNID is based on the development of new focal neurological signs, deterioration in the level of consciousness, or both, when the cause is felt to be ischemia attributable to vasospasm after other possible causes of worsening (e.g., hydrocephalus, seizures, metabolic derangement, infection, or excessive sedation) have been excluded [23]; as such, DCI is defined as the appearance of DNID and/or a new infarction on cerebral CT scan or magnetic resonance imaging (MRI), when the cause was attributed to vasospasm [23].

For patients with ICH, the following data are collected: ICH volume > 30 mL on the initial CT scan (measured/estimated by local neuroradiologist); the presence of intra-ventricular hemorrhage; location (deep, cortical, infratentorial); ICP monitoring within the first 48 h; and pupillary reactivity on arrival.

Daily data collection (only during the ICU stay) includes daily GCS score; Hb concentration (minimum and maximum); sodium and glucose levels at 8 am (or the first value of the day); ICP levels at 8 am (or the first value of the day); maximum ICP levels during the day; SOFA score; the presence of infection (location, pathogen, treatment); the presence of sepsis; the occurrence of serious adverse events (*see paragraph on adverse events*); the need for second-tier therapies for increased ICP (hypothermia; barbiturates; decompressive craniectomy) or seizures (convulsive or non-convulsive); and daily fluid intake and urine output (to calculate daily fluid balance).

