### Statistical methods: additional analyses

Subgroup analyses will be performed according to (a) underlying brain injury (TBI vs. SAH vs. ICH); (b) GCS at the moment of randomization (3–5; 6–8; 9–11); (c) presence of increased intracranial hypertension (defined as the need for specific therapies to reduce intracranial pressure [ICP]—if no ICP monitoring, then the patient is considered as not having intracranial hypertension); (d) age (< 45 years or ≥ 45 years); and (e) SOFA on randomization (< 8 and ≥ 8). Post hoc analyses will include (a) high- vs. middle- to low-income countries and (b) high-recruiting (i.e., > 25 patients) centers vs. others. All analyses will be processed by an independent statistician.

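### The intracranial-hypertension subgroup has no time anchor and codes every unmonitored patient as not having the condition

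*Protocol article*

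**What the plan says.** Statistical methods: additional analyses lists five prespecified subgroup factors. Two carry an explicit time point: "GCS at the moment of randomization (3–5; 6–8; 9–11") and "SOFA on randomization (< 8 and ≥ 8"). Injury type and age are baseline by nature. Intracranial hypertension is "defined as the need for specific therapies to reduce intracranial pressure [ICP"]), with no time window, followed by the rule "if no ICP monitoring, then the patient is considered as not having intracranial hypertension".

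Under Plans for assessment and collection of outcomes, the admission data contain no item for ICP-lowering therapy. The only such item is in the daily record: "the need for second-tier therapies for increased ICP (hypothermia; barbiturates; decompressive craniectomy"). That record is introduced as "Daily data collection (only during the ICU stay) includes daily GCS score" and is not limited to days before randomization. Monitoring appears as its own item only as "ICP monitoring within the first 48 h", although daily ICP values are also collected.

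The abstract gives the subgroup some prominence. It says the trial "will provide additional data in some subgroups of patients at high risk of brain ischemia, such as those with intracranial hypertension or cerebral vasospasm", and the main Discussion repeats the point in similar terms.

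**The concern.** A subgroup factor should be something the allocated treatment cannot change. A need for ICP-lowering therapy that may arise at any time in the ICU does not clearly meet that standard. Anemia can qualify a patient up to 10 days after injury (Table 1), and the transfusion thresholds then apply for up to 28 days (Interventions: description), so the daily therapy record overlaps the exposure period. ICU staff know the allocation, and the Objectives section expects better brain oxygenation in the liberal arm. An effect of allocation on the need for, or the decision to give, ICP-lowering therapy is thus conceivable, though the article does not claim one. If there is one, patients in the same subgroup but different arms are no longer comparable.

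The monitoring rule is a second problem, independent of the first. A patient whose ICP was never measured has unknown status, not normal pressure. Placing all such patients in the negative group mixes in true cases and pulls the two subgroup estimates together. It can also override the therapy-based half of the same definition: an unmonitored patient given one of the listed therapies for raised ICP would be coded negative.

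**Working it through.** The article gives no figure on this point, so there is none to reproduce. The text establishes the two features of the definition. The arithmetic below uses assumed inputs and shows only what could follow.

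**Step 1. Time anchor, factor by factor**

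| Factor | Time reference |
|---|---|
| Injury type | baseline by nature |
| GCS | randomization |
| Intracranial hypertension | none |
| Age | baseline by nature |
| SOFA | randomization |

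Intracranial hypertension is the only factor without an anchor.

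**Step 2. What follows if allocation changes the need for therapy**

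Suppose no patient's outcome depends on the arm, and overall poor outcome is 50% in both arms. Let a fraction *a* need therapy under either arm (poor-outcome risk *rₐ*), a fraction *d* need it only under arm C (risk *r_d*), and the rest never need it (risk *rₙ*). Arm T is the other arm.

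- Positive subgroup: risk is *rₐ* in arm T and (*a·rₐ* + *d·r_d*)/(*a* + *d*) in arm C.
- Negative subgroup: risk is [*d·r_d* + (1 − *a* − *d*)·*rₙ*]/(1 − *a*) in arm T and *rₙ* in arm C.

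Example with *a* = 0.25, *d* = 0.15, *rₐ* = 0.70, *r_d* = 0.50:

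- *rₙ* = (0.50 − 0.175 − 0.075)/0.60 = 0.417.
- Positive subgroup: 0.70 against (0.175 + 0.075)/0.40 = 0.625, a spurious difference of 7.5 points.
- Negative subgroup: (0.075 + 0.25)/0.75 = 0.433 against 0.417, a spurious difference of 1.7 points.

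The other cases took need at 40% in one arm and 25% to 37% in the other, *rₐ* of 65% or 70%, and *r_d* of 45% to 60%. The spurious difference ran from about 0.7 to 7.5 points in the positive subgroup and from about 0 to 4.2 points in the negative one. With need at 40% in both arms it is exactly 0. For scale, the Sample size section plans for an 11-point difference (50% to 39%).

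**Step 3. What follows from coding unmonitored patients as negative**

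Let *u* be the share unmonitored, *p* = 40% the prevalence among monitored patients, and *q* the prevalence among unmonitored patients. All three are assumptions. The share of true cases in the negative group is

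*f* = *u·q* / [(1 − *u*)(1 − *p*) + *u*].

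Suppose the true risk differences are −20 points with intracranial hypertension and −5 without, whether or not the patient is monitored. The true contrast is −15, and the contrast seen is −15 × (1 − *f*).

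| *u* | *f* at *q* = 10% | contrast seen | *f* at *q* = 40% | contrast seen |
|---|---|---|---|---|
| 10% | 0.01/0.64 = 1.6% | −14.8 | 0.04/0.64 = 6.3% | −14.1 |
| 20% | 0.02/0.68 = 2.9% | −14.6 | 0.08/0.68 = 11.8% | −13.2 |
| 40% | 0.04/0.76 = 5.3% | −14.2 | 0.16/0.76 = 21.1% | −11.8 |
| 60% | 0.06/0.84 = 7.1% | −13.9 | 0.24/0.84 = 28.6% | −10.7 |

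The result depends on *q* as much as on *u*. If clinicians monitor the patients they think at risk, *q* is below *p* and the left-hand columns are nearer the truth.

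**The case against.** The strongest reply is that this is a condensed article, and that the derivation window of a subgroup variable is the kind of detail an SAP supplies. A reader might infer that the trial will use therapies given after randomization to form the subgroup. The article does not say so: it fails to exclude them, and it does not state that the subgroup is derived from the second-tier therapies in the daily record. An SAP could add the anchor without contradicting anything. That limits the first part to what the definition admits as written. It does not remove it, because the same list anchors GCS and SOFA and leaves this factor open.

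A reader might also infer that the subgroup result will be biased. That needs allocation to affect ICP-lowering therapy. Expected gains in brain oxygenation do not establish this, and without such an effect Step 2 gives zero.

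The monitoring rule can be read as a deliberate requirement for both monitoring and therapy. That reading removes the internal contradiction but not the misclassification. If the 48-hour monitoring item is the one used, the rule would be largely unrelated to arm, so it would dilute the contrast and not confound it. This part, unlike the time anchor, is a rule the article states outright, and an SAP would have to depart from it.

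Finally, the abstract and Discussion promise additional data on this subgroup, not conclusions.

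**Conclusion.** The point holds in a limited form. Two features are on the page: no time anchor, and unknown ICP status recorded as absence. The first leaves the within-subgroup comparison unprotected only if transfusion strategy affects the need for ICP-lowering therapy, and the document gives no means of bounding that. The second dilutes the contrast: true cases would form about 2% to 29% of the negative group over the assumed ranges (10% to 60% unmonitored, prevalence 10% to 40% among them, 40% among the monitored). The upper end requires unmonitored patients to have intracranial hypertension as often as monitored ones, so it should not be quoted alone. One of five prespecified subgroup factors is affected, and the primary intention-to-treat analysis is not. The change is worth making because it is cheap and the article singles this subgroup out.

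**What to change.** - Define the subgroup by status at or before randomization, using therapy entries up to the day of randomization where the eCRF holds them.
- Check that first. Data management says an eCRF is generated for each randomized patient, the admission list has no ICP-therapy item, and the start of daily recording is not stated. With 791 of 794 patients already recruited (Trial status), new data collection is hardly an option.
- If pre-randomization therapy is not available, keep the analysis but label it as based on post-randomization information and exploratory.
- Name the therapies that count. Code a treated patient as positive whether monitored or not.
- Report the remaining unmonitored patients as a separate category, or keep the present coding and add a sensitivity analysis without them.

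The cost is a wording change in the analysis plan before unblinded analysis, plus a derivation from existing entries if they exist. The positive group will be smaller than under an any-time definition, and an extra category spreads the data more thinly.

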### Statistical methods: analysis to handle protocol non-adherence and any statistical methods to handle missing data

No specific analysis will be provided using the “per protocol” or “as treated” analysis set. Given our expectation that very few patients will crossover or be lost to follow-up, these analyses should agree very closely with the intention-to-treat analysis. No imputation will be performed for missing outcome data.

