#### Interventions: modifications

Protocol violation is defined as one of the following: (a) inability to maintain the daily max Hb values < 9 g/dL in the restrictive group and avoid transfusion until Hb drops below 7 g/dL OR > 9 g/dL in the liberal group for two consecutive days, (b) one or more transfusions given inappropriately (i.e., in contradiction of the assigned trigger level), and (c) error in type/cross-match between donor and recipient.

Crossover to another treatment arm than allocated is allowed based on the decision of the treating physician, such as (1) acute coronary syndrome, requiring a higher Hb level; (2) acute bleeding requiring multiple RBCT; and (3) lack of available blood. The reason for crossover or protocol violation will be mentioned in the electronic case report form (eCRF).

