### Sample size

The primary outcome measure of this study is the occurrence of unfavorable neurological outcome at 180 days, evaluated by a eGOS of 1–5. To calculate the sample size, we estimated a mortality rate of 15% and a percentage of poor neurological outcome of 35% (i.e., eGOS 1–5 of 50%). There are no specific epidemiological data to support this assumption, as the population is mixed (i.e., TBI, SAH, and ICH) and the proportion of patients being eligible for the study remains unknown. Thus, the initial sample size calculation identified a total of 2095 patients needed to be recruited for each arm to achieve a power of 90% at a two-sided alpha level of 0.05 or less to detect a reduction of poor outcome rate at 180 days from 50 to 45% (absolute reduction of 5%, i.e., 10% relative reduction) in one of the two arms. Sample size calculation was adjusted twice. The first change (approved in August 2019) consisted in considering a reduction in unfavorable neurological outcome rate at 180 days from 50 to 40% (absolute reduction of 10%, i.e., 20% relative reduction, *n* = 1000) in one of the two arms, considering the relatively low number of patients being eligible for the study. The second change (approved in June 2022) consisted in considering a reduction in unfavorable neurological outcome rate at 180 days from 50 to 39% (absolute reduction of 11%, i.e., 22% relative reduction, *n* = 756–378 patients per group) in one of the two arms, with a power of 85% and at a two-sided alpha level of 0.05. Considering a potential 5% lost to follow-up, a total of 794 patients (397 per group) are needed to complete the study. This last modification was decided because of the coronavirus disease 2019 (COVID-19) pandemic, which significantly disrupted recruitment and blood availability and led to uncertainty over future recruitment.

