Data on each transfused RBC unit during the ICU stay and premature study termination (documenting the reason and time of termination) are recorded. In case of death, reasons for withdrawal of care are collected. ICU and hospital lengths of stay, the duration of mechanical ventilation over the first 28 days (either by endotracheal tube or tracheostomy), the need for tracheostomy on ICU discharge, and location of discharge after a hospital stay (home vs. rehabilitation vs. nursing home) are recorded. Follow-up at 180 days for primary outcome measure assessment is performed.

Data will be collected and stored as described at point 19, into the eCRF. After 6 months, patients who are still alive will be contacted by phone or by face-to-face meeting, according to local practice, for a structured interview to obtain the eGOS scale. The eGOS is widely used to assess neurological outcome in this setting [19].

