### Statistical methods: outcomes

Analysis of data is based on intention-to-treat. Statistical analysis will be performed using the last version of SPSS for Windows (Chicago, USA). Continuous variables will be summarized using medians and quartiles and analyzed using a Wilcoxon rank sum test. Categorical variables will be analyzed using the Fisher exact test. The primary outcome comparisons will be analyzed using a chi-square analysis and reported as an absolute risk reduction of poor outcome and its corresponding 95% confidence interval. The primary outcome will also be adjusted for pre-specified covariates (stratification criteria) and presented for each category of brain injury (TBI, SAH, ICH).

All secondary outcomes will be analyzed using independent samples *t*-tests, chi-square test, as appropriate, without additional adjustment. For 28-day mortality, the Cox proportional hazard model will be used to determine time-to-event hazard ratios and 95% confidence intervals.

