### Informed consent

Written informed consent must be obtained prior to the randomization to the study. Because of the difficulties predicting the exact moment at which anemia may occur during the ICU stay, it is recommended that written informed consent be obtained as soon as possible after ICU admission so that randomization can be performed rapidly when the inclusion criteria are met. For patients who are unable to consent, their legal representatives are informed of the study as soon as possible and must sign for participation in the trial before randomization. Subjects with sufficient neurological recovery are informed of their study participation and be asked to provide their consent for the use of their data. Patients or next of kin can withdraw consent at any time during the study without giving a specific reason. Withdrawal should not influence the standard of care, with an Hb threshold for RBC transfusion that will then be decided by the attending physician. Patients withdrawing from the study are asked to consent for the inclusion of data collected before withdrawal. The site investigator may also withdraw a subject from the study for safety reasons (e.g., acute myocardial infarction needing higher Hb levels).

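### The primary analysis is labelled intention-to-treat, but the no-imputation rule makes it complete-case, and the follow-up and analysis status of withdrawn patients is not stated

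*Protocol article*

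**What the plan says.** All references are to the protocol article.

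- *Statistical methods: outcomes*: "Analysis of data is based on intention-to-treat". The same section fixes the primary test: "The primary outcome comparisons will be analyzed using a chi-square analysis and reported as an absolute risk reduction of poor outcome".
- *Statistical methods: analysis to handle protocol non-adherence and any statistical methods to handle missing data*: "No imputation will be performed for missing outcome data". Per-protocol and as-treated analyses are also ruled out, on the expectation that crossovers and losses will be rare.
- *Study outcomes*: death is level 1 of the eGOS and so counts as unfavourable.
- *Plans for assessment and collection of outcomes*: at six months, "patients who are still alive will be contacted by phone or by face-to-face meeting". *Plans to promote participant retention and complete follow-up* adds repeated contact attempts and recourse to the general practitioner.
- *Informed consent*: "Subjects with sufficient neurological recovery are informed of their study participation and be asked to provide their consent for the use of their data". Withdrawal is open at any time to the patient or the family, and those who withdraw are asked to let data gathered up to that point be kept. The section also says: "The site investigator may also withdraw a subject from the study for safety reasons (e.g., acute myocardial infarction needing higher Hb levels".
- *Interventions: modifications*: "Crossover to another treatment arm than allocated is allowed based on the decision of the treating physician, such as (1) acute coronary syndrome".
- *Sample size*: "Considering a potential 5% lost to follow-up", the total rises from 756 to 794.

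**The concern.** Intention-to-treat means that every randomised patient is analysed in the assigned arm. A chi-square test on the dichotomised eGOS with no imputation drops anyone without an eGOS, so the label and the method differ. This is an explicit rule that closes off imputation. It is not a detail left open for an analysis plan.

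The dropped patients may not be a random sample. A known death always has an outcome, whereas a survivor has one only if reached. Only patients who recover well enough are asked to agree to use of their data, so refusals at that step would come from the better outcomes. Other routes act the other way: a patient lost after discharge may have died unknown to the site, and next of kin may withdraw a patient who is doing badly.

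Withdrawal is a separate problem. Two sections give similar coronary events different dispositions. The crossover route keeps the patient in the trial. The withdrawal route takes the patient out of it, and nothing shown says whether such a patient is followed to day 180 or how the patient is counted. Acute myocardial ischaemia is on the serious adverse event list, whose events were chosen for a possible relation to transfusion, and treating staff know the allocation. Withdrawal could therefore differ by arm. At stake is the validity of the primary risk difference.

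**Working it through.** **Inputs.** From *Sample size*: 50% against 39% unfavourable, 15% mortality (one overall figure, assumed here for both arms), 85% power, two-sided 0.05, 5% loss, 397 per arm. All missingness patterns below are assumptions; the article gives none.

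**The plan's own figure.** The usual two-proportion formula gives 365 per group without continuity correction and 383 with it. The stated 378 lies between and is within 1.3% of the latter. For losses, 756 × 1.05 = 793.8, which is the stated 794. A 5% loss is about 0.05 × 794 = 40 patients, or 20 per arm, leaving 397 × 0.95 = 377.

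**Formula.** Complete-case unfavourable rate = (deaths + observed unfavourable survivors) / (all observed).

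**A. 5% of each arm missing, same mechanism in both arms**
- Equally likely for all survivors (0.05/0.85 = 5.88% of them):
  - higher-rate arm: (0.15 + 0.35 × 0.9412)/0.95 = 50.5%
  - lower-rate arm: (0.15 + 0.24 × 0.9412)/0.95 = 39.6%
  - difference 10.9 points, a shift of 0.1.
- Favourable survivors only: 0.50/0.95 − 0.39/0.95 = 52.6% − 41.1% = 11.6 points, a shift of 0.6.
- Unfavourable survivors only: 0.45/0.95 − 0.34/0.95 = 47.4% − 35.8% = 11.6 points, a shift of 0.6.
- With no true effect (50% in both arms), all three give a difference of 0.

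**B. 2% against 8% missing, spread evenly over survivors, no true effect**
- 2% arm: (0.15 + 0.35 × (1 − 0.02/0.85))/0.98 = 50.2%
- 8% arm: (0.15 + 0.35 × (1 − 0.08/0.85))/0.92 = 50.8%
- Spurious difference 0.6 points; type I error stays at about 5%.

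**C. 2% against 8% missing, every loss a favourable survivor, no true effect**
- 0.50/0.98 = 51.0% and 0.50/0.92 = 54.3%: a spurious 3.3 points, or 3.3/11 = 30% of the target.
- Analysed: 397 × 0.98 = 389 and 397 × 0.92 = 365. Standard error = √(0.510 × 0.490/389 + 0.543 × 0.457/365) = 0.0364; z = 0.0333/0.0364 = 0.92. Chance of |z| > 1.96 is about 15%.
- The milder 3% against 7%: 0.50/0.93 − 0.50/0.97 = 2.2 points, type I error about 9%.

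**D. 5% missing per arm, fully opposite mechanisms**
- At the 11-point effect: 47.4% − 41.1% = 6.3 points, or 52.6% − 35.8% = 16.8 points. At 377 per arm, power falls from 86% to 41.5% in the first case.
- With no true effect: 52.6% − 47.4% = 5.3 points.

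**E. Logical bounds.** Suppose complete cases show 50% against 39%, with 5% missing per arm.
- Lower bound: 0.95 × 0.50 − (0.95 × 0.39 + 0.05) = 5.5 points.
- Upper bound: (0.95 × 0.50 + 0.05) − 0.95 × 0.39 = 15.5 points.

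**The two coronary rules side by side.** *Interventions: modifications* lists acute coronary syndrome as a ground for crossover. *Informed consent* offers acute infarction as an example of a ground for withdrawal by the investigator. One patient could fit both. The sentence about keeping earlier data concerns patients who withdraw; it says nothing of patients whom the investigator withdraws.

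**The case against.** The strongest case on the other side is that about 5% loss, with death inside the endpoint, is modest. Complete-case analysis supported by a sensitivity analysis is then defensible, and sensitivity analyses are commonly left to an analysis plan that is not shown. Day-180 assessors are blinded, contact attempts are repeated, and nothing in the article indicates that losses will differ by arm. The 15% type I error needs a fourfold difference in loss and requires that 0.08/0.50 = 16% of favourable survivors in one arm be lost but no unfavourable ones.

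Most of this stands. The absence of a sensitivity analysis from the article is not itself a fault, and making multiple imputation the primary analysis is a debatable choice at this level of loss. What remains is the explicit no-imputation rule under an intention-to-treat label, and the unreconciled withdrawal text.

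A reader might go further in four ways that the article does not support:

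- *Only survivors can be missing.* The article says that deaths score 1 and that living patients are contacted. It does not say that every death will be known.
- *Exclusions depend on outcome.* That is a possibility, not something shown; for infarction the dependence would be on an intermediate event.
- *Patients withdrawn by the investigator leave the analysis.* The text does not say so. It describes withdrawal partly as a return of the transfusion threshold to the attending physician, which can be read as a change of treatment only.
- *Expecting very few losses contradicts the 5% allowance.* A potential 5% is an ordinary planning margin.

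**Conclusion.** The point holds in a limited form. As written, the primary analysis is complete-case under an intention-to-treat label. Outcome-related missingness is plausible, in either direction, and the status of withdrawn patients is unclear.

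The size depends wholly on assumed missingness and on 15% mortality in both arms. If the mechanism and the rate are the same in both arms at 5%, the bias is nil under no effect and 0.1 to 0.6 points at the 11-point effect. It becomes material only if missingness differs by arm: 0.6 points for unequal but even loss among survivors, 3.3 points in the extreme favourable-only case, and 5 to 6 points for fully opposite mechanisms. Nothing in the article shows such a difference. Open-label care and a withdrawal ground that the assigned strategy might influence mean that it cannot be excluded either. This should be fixed, but it does not invalidate the design.

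**What to change.** 1. Reconcile *Interventions: modifications* with *Informed consent* on coronary events. State that ending the assigned strategy does not end follow-up: every randomised patient is followed to the 180-day eGOS and analysed as randomised, unless consent is refused. The clinical decision itself is left as it is. Report refusals and withdrawals by arm.
2. Replace the blanket no-imputation sentence with a pre-specified analysis of all randomised patients, at least as a sensitivity analysis beside the complete-case result. Set known deaths to eGOS 1. Multiply impute missing eGOS by arm from the stratification factors and covariates already planned for the eCRF, such as age, daily ICU GCS and discharge location. With 72 centres, centre would need grouping or a random effect. Add a tipping-point analysis that varies the imputed outcomes separately in each arm.

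The cost is a few sentences of wording and modest programming, with no new data items. With 791 of 794 patients already recruited according to *Trial status*, the follow-up wording can help only patients whose day-180 assessment can still be obtained. The analysis change can be made in full if it is fixed before the data are examined by arm.
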